### Reporting of serious adverse events (SAE) and other safety related events

The events will be reported on the CRF(side effects) by the person conducting the experiment during the experiment. Due to the short half-life period of caffeine no reporting after the testing is intended.

In case of any health related problems at the same day as the testing day, the subjects will be requested to inform the sponsor investigator [name] by phone.

Reporting of SAEs

All SAEs must be reported immediately and within a maximum of 24 hours to the Sponsor-Investigator of the study. The Sponsor-Investigator will re-evaluate the SAE and return the form to the site.

SAEs resulting in death are reported to the local Ethics Committee (via local Investigator) within 7 days.

Reporting of SUSARs

A SUSAR needs to be reported to the local Ethics Committee (local event via local Investigator) and to Swissmedic for category B and C studies (via Sponsor-Investigator) within 7 days, if the event is fatal, or within 15 days (all other events).

Reporting of Safety Signals

All suspected new risks and relevant new aspects of known adverse reactions that require safety-related measures, i.e. so called safety signals, must be reported to the Sponsor-Investigator within 24 hours. The Sponsor-Investigator must report the safety signals within 7 days to the local Ethics Committee (local event via local Investigator).

Periodic reporting of safety

No periodic reporting is intended.

### Follow up of (Serious) Adverse Events

No follow-up period is intended due to the short half-life period of caffeine (max 5 h).

# STATISTICAL METHODS

This study is a pilot-study with a small sample size. Therefore, normal distribution of the data cannot be assumed. Descriptive statistics, i.e. median, 25/75% quartiles, 95% confidence intervals and range, will be used. A p-value of < 0.05 will be considered significant, even though multiple hypotheses will be tested.

The treatment period (i.e. sequence of placebo and caffeine treatment) will not be included into the statistical analysis, because the wash-out period (48h) is considered more than long enough to prevent any carry-over effect. Furthermore, the period effect is considered to be negligible, because study participants will undergo a training session before the collection of data in order to avoid any learning effect.

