| Ho | Null hypothesis |
| H1 | Alternative hypothesis |
| HFG | Humanforschungsgesetz (Law on human research) |
| HMG | Heilmittelgesetz |
| HRV  IMP | Heart rate variability  Investigational Medicinal Product |
| IIT | Investigator-initiated Trial |
| ISO | International Organisation for Standardisation |
| ITT | Intention to treat |
| KlinV | Verordnung über klinische Versuche in der Humanforschung |
| LHR | Law on human research |
| LPTh | Loi sur les produits thérapeutiques |
| LRH | Loi fédérale relative à la recherche sur l’être humain |
| MD | Medical Device |
| OClin | Ordonnance sur les essais cliniques dans le cadre de la recherche sur l'être humain |
| PI  RPE | Principal Investigator  Rate of perceived exertion |
| SDV  SCI | Source Data Verification  Spinal Cord Injury |
| SOP | Standard Operating Procedure |
| SPC | Summary of product characteristics |
| SUSAR | Suspected Unexpected Serious Adverse Reaction |
| TMF | Trial Master File |

Study schedule

| Study Periods | Recruitment | Screening and Familiarization | Intervention Period | |
| --- | --- | --- | --- | --- |
| Visit | 1 | 2 | 3 | 4 |
| Time | individual | individual | 09:00 | 09:00 |
| Patient Information and Informed Consent | X | - | - | - |
| Subject Group | X | X | X | X |
| Medical History | X | - | - | - |
| In- /Exclusion Criteria | X | - | - | - |
| Checklist | - | - | X | X |
| VO_2max_ Test | - | X | - | - |
| Vital Signs | - | - | X | X |
| Laboratory Tests (Catecholamine) | - | - | X | X |
| Randomisation | X | - | - | - |
| HRV Measurement | - | - | X | X |
| 3 min Performance Test | - | X | X | X |
| Tidal Volume Measurement | - | - | X | X |
| Venous Blood Sample | - | - | X | X |
| Capillary Blood Sample | - | - | X | X |
| Blood Glucose Level | X | - | - | - |
| Blood Pressure Measurement | - | - | X | X |
| Ingestion of Caffeine or Placebo | - | - | X | X |
| Adverse Events | - | - | X | X |

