## Methods of minimising bias

### Randomisation

Randomisation will be assessed by lot. 50 % of all the subjects will first conduct the placebo trial and the other 50% first the caffeine trial. With which trial they start will be assigned by lot. So, there will be an “A” lot and a “B” lot and the fortune will decide whether they have the A or the B trial first. The test administrator only knows whether they have to ingest supplement A or supplement B but he does not know which supplement it is.

Applying a significance level of 0.05 and a power of 0.8 with a difference of 7.59 and a standard deviation of 10 Watt, we receive a total sample size of 9. With inclusion of a 10% drop-out rate we obtain a total sample size of 10 subjects per group. With the three different groups (able-bodied, paraplegic and tetraplegic subjects) we have in total 30 subjects and thus 120 visits overall.

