## Assignment to study groups

50 % of all the subjects will first conduct the placebo trial and the other 50% first the caffeine trial. With which trial they start will be assigned by lot. So, there will be an “A” lot and a “B” lot and the fortune will decide whether they have the A or the B trial first. The test administrator only knows whether they have to ingest supplement A or supplement B but he don`t know which supplement it is.

Each participant gets a number, his study ID. This ID will be written on every CRF to identify the participant. The participants name with his convenient ID will be stored in a sealed envelope to be sure that anonymity is given.

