## Procedures at each visit

**Recruitment:** The subject is visiting the Institute of Sport Medicine in Nottwil for the first time during the study period. Together with the subject the informed consent is filled in. After that the health questionnaire is answered and we check if all the inclusion and exclusion criteria are fulfilled including a blood glucose testing.

**Screening:** The subject performs a VO_2max_-Test on the arm crank ergometer for measuring the maximal rate of oxygen consumption. After that the subject has a 20-30 min break. Then the 3 min performance test of the following two testing day is carried out for familiarization purposes.

**Testing Day 1:** The subject arrives at 09:00 at the Institute of Sport Medicine in Nottwil. The check list is worked trough. After that the subject is requested to empty his bladder and in case of compression stockings to take them off. Then he puts on the heart rate belt and transfers himself in a supine position on a couch where a breathing mask is put on his mouth and his nose. The HRV and tidal volume measurements are performed. Then the breathing mask is taken off followed by taking of a blood sample at the crook of the arm and the ingestion of the capsules filled with caffeine or placebo. After that the subject has a 40 min break whereas it is not allowed to be physical active or to consume any beverage or food. According to this break, the breathing mask is put on again and the second HRV and tidal volume measurement is performed. After that a second venous blood sample is taken. Then the subject transfers himself to the arm crank ergometer where a short warming up is performed followed by taking a capillary blood sample on the ear lobe for analysing the amount of blood lactate. Then the 3 min all out performance test is performed. Afterwards the subject’s capillary blood is taken again and he has 5 min for transferring himself again on the coach and the HRV and tidal volume is measured for the last time. After this, the breathing mask and the heart rate belt are taken off.

**Testing Day 2:** The procedure of this second testing day is the same as on testing day 1 (see above) except to the kind of capsule which the subject has to ingest. So if the subject ingested the caffeine capsules on the first testing he has now to ingest the placebo capsules or the other way round.

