## Planned Analyses

### Datasets to be analysed, analysis populations

Only data from subjects who have completed the whole study protocol will be used for analysis. For each group, a minimum of 10 data sets will be analysed.

Analyses will be performed separately for the three subject groups (i.e. tetraplegic, paraplegic, able-bodied). No direct comparison between the groups will be performed.

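### Period is left out of the crossover analysis and sequence is not balanced within the groups analysed, so a period effect would bias any group with an unequal split and cost power in an equal one

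*Protocol*

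**What the plan says.** Section 11 (Statistical Methods) states that "The treatment period (i.e. sequence of placebo and caffeine treatment) will not be included into the statistical analysis". It gives two reasons. The first concerns carry-over: "because the wash-out period (48h) is considered more than long enough to prevent any carry-over effect". The second concerns period itself: "the period effect is considered to be negligible, because study participants will undergo a training session before the collection of data".

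Section 6.2.1 (Randomisation) sets the allocation: "50 % of all the subjects will first conduct the placebo trial and the other 50% first the caffeine trial". Section 7.3 repeats it and adds "With which trial they start will be assigned by lot". Neither section mentions balance within the three subject groups.

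Section 11.4.1 then says "Analyses will be performed separately for the three subject groups (i.e. tetraplegic, paraplegic, able-bodied". Section 11.4.2 applies a Wilcoxon signed-rank test to caffeine against placebo in each group, with no period or sequence term. Section 11.5 keeps full data sets only and replaces drop-outs, without saying which sequence a replacement follows.

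The training session is described in section 9.3. It is a single run of the 3 min test at the screening visit, after the VO2max test: "After that the subject has a 20-30 min break", and then the familiarisation run. The HRV procedure is not rehearsed.

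**The concern.** A crossover compares each man with himself on two days, so any systematic difference between the first and second day (practice, training state, familiarity with the laboratory) sits in his paired difference. It cancels from a group's mean only if equal numbers take caffeine first and second in that group. The protocol promises equality at the level of all subjects, but draws its conclusions group by group.

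The two reasons given do not settle this. Wash-out deals with carry-over, not with period. The training session does bear on period, but one run after a maximal test supports the claim of a negligible effect without any figure. It does not touch HRV, the second primary outcome.

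At stake is the caffeine estimate in each group, and power that is already modest.

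**Working it through.** **Inputs from the protocol.** Ten per group, 30 in all (synopsis, 6.2.1); two-sided tests at 0.05 (11, 11.1); difference 7.59 W and SD 10 W (6.2.1); signed-rank test (11.4.2).

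**Assumed.** The 10 W is the SD of the paired differences (6.2.1 does not say which SD it is). The period effect π, the mean change from first to second test day apart from treatment, is given nowhere; I use 2, 3.8 (half of 7.59), 5 and 7.59 W.

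**The plan's own figure.** Section 6.2.1 reports 9 per group for 80% power, then 9/(1 − 0.1) = 10. The second step reproduces. The first does not with these inputs: ((1.96 + 0.842) × 10/7.59)² = 13.6, so 14 by the normal formula and 16 by the paired t test. Nine results from the two-sided paired t test if the SD of differences is about 7.1 W. Hence the baseline power below is about 55%, not 80%. The present point does not depend on this.

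**Chance of an unequal split.** With 15 of 30 per sequence, the number of placebo-first men in a group of 10 is hypergeometric.
- One group is 5:5: C(10,5) × C(20,10)/C(30,15) = 0.30; 7:3 or worse: 0.245.
- All three are 5:5: C(10,5)³/C(30,15) = 0.103, so at least one is unequal with probability 0.897.
- At least one is 7:3 or worse: 0.467; 8:2 or worse: 0.122.
- If the lot is a simple independent draw, one group is 7:3 or worse with probability 0.344, and at least one of three with 1 − (1 − 0.344)³ = 0.72.
- With the 36 subjects of section 11.2, all three groups are 6:6 with probability 0.087.

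**Bias.** For a man taking placebo first, the caffeine-minus-placebo difference is the caffeine effect plus π; for a man taking caffeine first, it is the caffeine effect minus π. The mean is therefore shifted by π × (placebo-first − caffeine-first)/n: 0 at 5:5, 0.2π at 6:4, 0.4π at 7:3, 0.6π at 8:2. For π = 3.8 W that is 0.8, 1.5 and 2.3 W. The sign depends on which sequence is over-represented.

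**Power at 5:5.** The shifts cancel in the mean but widen the differences: their SD becomes √(10² + π²), which is 10.2, 10.7 and 12.6 W for π = 2, 3.8 and 7.59 W. Simulated exact signed-rank test (n = 10) against a period-adjusted t analysis:

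| π (W) | Signed-rank power for 7.59 W, 5:5 | Period-adjusted power, 5:5 | Signed-rank type I error: 5:5 | 7:3 | 8:2 |
|---|---|---|---|---|---|
| 0 | 55% | 56% | 5% | 5% | 5% |
| 2 | 54% | 56% | 4.5% | 5% | 6% |
| 3.8 | 49% | 56% | 4% | 6% | 8% |
| 7.59 | 34% | 56% | 1.5% | 6% | 15% |

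If the imbalance works against caffeine, signed-rank power at π = 3.8 W is 34% at 7:3 and 28% at 8:2.

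**Averaged over the lot.** Type I error is 0.041 (π = 5 W) and 0.035 (7.59 W). Power falls from 0.55 to 0.46 and 0.36.

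**After adjustment.** The period-adjusted estimate is unbiased at every split, with type I error near 5%. Its power does not depend on π but does depend on the split: 56% at 5:5, 54% at 6:4, 49% at 7:3, 39% at 8:2.

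**The case against.** The best defence is that the protocol considered period and gave a reason for it separate from wash-out, that subjects rehearse the same 3 min test beforehand, and that no figure in the document shows a practice effect after that. This stands as far as it goes. The size of the effect is unknown, and at 2 W the loss in a 5:5 group is only one or two points of power. The point is that the assumption is unsupported and guarding against it is cheap.

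For HRV, section 11.1 compares changes from a same-day baseline. That removes an additive shift between days, though not a period effect on the change itself. The figures above should not be carried over to HRV.

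Sections 6.2.1 and 7.3 do not exclude balance within groups, and a separate randomisation procedure might provide it. As written, the protocol does not promise it.

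A reader might infer three stronger things that the document does not support:
- *Every group's estimate is biased.* It is not: a 5:5 group, about 30% of the time, has none.
- *The false-positive rate is inflated.* The 15% needs both an 8:2 split (8:2 or worse is about 5% per group) and a period effect as large as the whole planned caffeine effect. Over the lot the test is slightly conservative. That average is limited comfort, since the trial makes one draw and reads each group on its own.
- *Randomisation precedes the eligibility check.* The study schedule puts inclusion and exclusion criteria and blood glucose at the same first visit; the visit labelled screening holds the VO2max test and familiarisation.

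**Conclusion.** The point holds conditionally. Nothing in the stated design or analysis keeps a period effect out of a group's caffeine estimate when the split is unequal, and some group will probably be unequal (0.90 with 15:15 overall). The bias is 20%, 40% or 60% of the period effect at 6:4, 7:3 or 8:2, in either direction and zero on average. The more dependable cost is power, which an ignored period effect lowers even at 5:5. How much either matters rests on a period effect that the protocol does not quantify and on reading 10 W as the SD of the paired differences. It is worth correcting in a pilot because section 11.1 still specifies significance tests of primary hypotheses in each group.

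**What to change.** In sections 6.2.1 and 7.3, draw the lot separately within each subject group with equal numbers per sequence (5:5, or 6:6 if the 36 of section 11.2 are enrolled). State that a replacement takes the sequence of the man he replaces.

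In section 11, replace the sentence excluding period with, for example: *In each group the caffeine effect will be estimated from a linear model with subject, period and treatment, reported alongside the Wilcoxon signed-rank test.* Say in advance which of the two decides the hypothesis.

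The two changes belong together. Balance alone removes the bias of the mean but leaves the signed-rank test losing power; adjustment alone is unbiased but loses power as the split worsens.

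The cost is three lots instead of one, one degree of freedom, and a normality assumption that section 11 is reluctant to make. At 5:5 with no period effect, power is about 55 to 56% either way. A rank-sum test on period differences between sequences would avoid the normality assumption but is not free: about 44% power at 5:5, better than the signed-rank test only when the period effect is large (44% against 34% at 7.59 W).

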## Hypothesis

In order to investigate the effect of caffeine on the performance and the HRV, the two following primary hypotheses will be tested:

1. H_0_: m_1_ = m_2_ versus
   H_1_: m_1_ ≠ m_2_
   where m_1_ = performance (power output) under placebo
    m_2_ = performance (power output) under caffeine

   This hypothesis will be tested for the three subject groups (i.e. tetraplegic, paraplegic, able-bodied).
2. H_0_: m_1_ = m_2_ versus
   H_1_: m_1_ ≠ m_2_
   where m_1_ = change in HRV from baseline to post-treatment under placebo treatment
    m_2_ = change in HRV from baseline to post-treatment under caffeine treatment

   This hypothesis will be tested for the three subject groups (i.e. tetraplegic, paraplegic, able-bodied).

## Determination of Sample Size

This study represents a pilot study and therefore no power analysis was performed.

A total of 36 subjects who are classified into 3 groups (tetraplegic, paraplegic, able-bodied) will be included which includes an over-recruitment by approximately 20% to take into account possible drop-outs. A minimum of 10 data sets will be required for each subject group.

## Statistical criteria of termination of trial

Not applicable

## Planned Analyses

### Datasets to be analysed, analysis populations

Only data from subjects who have completed the whole study protocol will be used for analysis. For each group, a minimum of 10 data sets will be analysed.

Analyses will be performed separately for the three subject groups (i.e. tetraplegic, paraplegic, able-bodied). No direct comparison between the groups will be performed.

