## Investigational Product (treatment, device) and Indication

Caffeine is a substance found naturally in the leaves, beans and fruits of a variety of plants and is regularly consumed by ~90% of adults. The most common dietary source of caffeine is coffee but also coca cola and energy drinks contain a high amount of caffeine.

Until 2004, caffeine was on the list of banned substances with a critical value. But then caffeine was removed from this list because of further knowledge on performance enhancing effects of caffeine at specific doses. They realized that higher doses act as performance inhibiting substances.

Caffeine is absorbed within 30 to 45 min and it exerts a variety of different effects on our body. The major effects of caffeine are an enhanced muscle contraction, elevation of epinephrine and norepinephrine and so acting as a stimulant influencing bronchodilatation, higher alertness and suppressing fatigue.

A variety of different studies showed performance enhancing effects of caffeine on exercise performance of aerobic but also on short term, high-intensity anaerobic performance. Most of the people respond with a performance enhancing effect but others act as non-responders or show some negative effects. Thus effects of caffeine intake depend on the regularity of caffeine consume as habitual consumers benefit less from caffeine intake before exercise performance. New considerations for athletes indicate to abstain from caffeine one week before the competition to get the best possible benefit from caffeine consumption.

Caffeine is classified as an A supplement which means that scientific experience showed some performance enhancing effects in a healthy trained population group. No supplement on the A-list is considered as a performance enhancing product in all situations, sports or in all different population groups.

In very high doses (>6 mg/kg body mass) caffeine can provoke some adverse effects. Side effects are known as tachycardia, tremor, sleep disturbances, headache and irregular heart rate. As our doses will be lower than these high doses such side effects won`t be expected.

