## Criteria for withdrawal / discontinuation of participants

Subjects have to be withdrawn if they won`t sign the written informed consent or if they won`t fulfil the study criteria. There is a definition of some criteria (sleep, nutritional intake 12h before the test, training intensity of previous training sessions, caffeine intake before the test, etc.). If these criteria won`t be fulfilled, then we have to withdraw the subjects from our trials.

Other reason for withdrawal would be if diseases occur or if the participant suffers from high gastrointestinal side effects or even some worse health problems because of the caffeine intake. If a participant is in danger, we have to withdraw him from our study for safety reasons.

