## Dose / Device modifications

The dose won`t be changed. If there are any problems with the ingested dose, we will exclude the participant from the study.

As the caffeine dose is just administrated once we cannot change the dose during the study protocol.

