## Data Collection and Follow-up for withdrawn participants

If a subject withdraws after session 1 or session 2 we will collect data but won`t use it in our analysis because of the missing data for session 3. Therefore, already collected data will be destroyed.

As we have no follow-up part for this study we won`t collect any data of withdrawn subjects.

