## Handling of missing data and drop-outs

All available data will be analysed and no missing data will be replaced. Only data from full sets of data will be analysed and drop out will be replaced by new study participants.

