### Analysis and archiving

Anonymized data will be exported from the data management system for analysis in statistic software.

Electronic data will be stored in an electronic archive maintained and controlled by the IT department of the Swiss Paraplegic Centre. Electronic data will not be deleted. Source data and identification data will be stored in a locked archive room with limited access for a minimum of 10 years.

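### Men withdrawn for side effects are replaced, left out of the completers-only analysis and in part have their data destroyed, against the protocol's own archiving rule, so the power-output result applies only to men who tolerated the dose and cannot be checked

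*Protocol*

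**What the plan says.** - **Withdrawal (7.4, 8.3).** Among the grounds for withdrawal is "if the participant suffers from high gastrointestinal side effects or even some worse health problems because of the caffeine intake". Section 8.3 adds: "If there are any problems with the ingested dose, we will exclude the participant from the study". Section 7.4 also lists grounds unrelated to the capsule, such as sleep, nutrition, training and prior caffeine intake.
- **Analysis set (11.4.1).** "Only data from subjects who have completed the whole study protocol will be used for analysis". At least ten data sets per group are required, and the primary power-output test is a within-subject Wilcoxon signed-rank test in each group (11.4.2).
- **Replacement (11.5).** "Only data from full sets of data will be analysed and drop out will be replaced by new study participants". The sentence just before it says that all available data are analysed and that missing values are not replaced.
- **Data of withdrawn men (8.5).** For men who leave after session 1 or 2: "Therefore, already collected data will be destroyed"
- **Archiving (12.1.3, 12.2.3).** All study data are kept for at least ten years. On electronic records: "Electronic data will not be deleted"
- **Expected response (3.2).** "Most of the people respond with a performance enhancing effect but others act as non-responders or show some negative effects"

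**The concern.** Two problems stand in the text.

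First, the protocol gives incompatible instructions on data. A team following section 8.5 would destroy records that sections 12.1.3 and 12.2.3 require it to keep. This cannot be undone: no later analysis plan can recover them.

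Second, the rules together form a selection step linked to treatment. A man who cannot tolerate the caffeine session leaves the study, drops out of the analysis set and is replaced, so the group again shows ten complete pairs. The overall objective (4.1) asks whether caffeine is an ergogenic aid in spinal cord injured subjects. The planned test answers that for men who tolerated the dose and finished both sessions. If the men lost would have performed worse on caffeine, the estimate is too favourable, and with their records gone the loss cannot be examined.

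**Working it through.** **1. The documents side by side**

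| Topic | One statement | Other statement |
|---|---|---|
| Data already collected from withdrawn men | 8.5: destroyed | 12.1.3: all study data kept at least ten years; 12.2.3: electronic data not deleted |
| Data analysed | 11.5, first sentence: all available data | 11.5, second sentence, and 11.4.1: full sets from completers only |

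Neither conflict needs an assumption.

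**2. Reach of the destruction rule.** Section 6.1 counts three test sessions, the first being screening and familiarisation. Section 8.5 gives the missing session 3 as its reason. On that numbering it covers men with at most one dosed session. A man who stops during the last dosed session is lost through the completers rule instead.

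**3. Room for losses.** Section 11.2 recruits 36 men in three groups: 36 / 3 = 12 per group, against a minimum of 10. So 12 − 10 = 2 spare places per group, and 12 / 10 = 1.2, which reproduces the stated over-recruitment of about 20%. These places cover drop-outs for any reason. Taking 0 to 2 of them as intolerance is an assumption.

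**4. Direction and size of the selection effect.** Let p be the share of men withdrawn for intolerance in the caffeine session, and L the amount by which their caffeine-minus-placebo difference is worse than that of the tolerators (mean μ). The mean over all men is (1 − p)μ + p(μ − L) = μ − pL, so completers exceed all men by pL. If a share q is also withdrawn for complaints in the placebo session, and their difference would have been more favourable to caffeine by M, the net shift is pL − qM.

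The documents give none of p, L, q or M. With q = 0 and assumed ranges p = 5 to 20% and L = 0 to 20 W:

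- L = 0: shift 0 W
- p = 5%, L = 10 W: 0.5 W
- p = 10%, L = 10 W: 1.0 W
- p = 10%, L = 20 W: 2.0 W
- p = 20%, L = 20 W: 4.0 W, or 4.0 / 7.59 = 53% of the difference used in section 6.2.1

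Suppose the true mean over all men is zero and the SD of the paired difference is 10 W (also assumed). The simulated chance per group of a false result in favour of caffeine is then about 2.5% with no selection, 3.3% at (5%, 10 W), 4.5% at (10%, 10 W), 8.0% at (10%, 20 W) and 20% at (20%, 20 W).

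**5. Worst-rank bound.** The exact two-sided signed-rank p-value is 2 × (number of rank subsets with sum ≤ W) / 2^n, where W is the sum of ranks against caffeine. Each man stopped in the caffeine session is given the next largest rank against caffeine.

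| Completers' result | Ten completers | One such man added | Two added |
|---|---|---|---|
| W = 8 | 2 × 25 / 1024 = 0.049 | W = 19: 2 × 246 / 2048 = 0.240 | W = 31: 2 × 1166 / 4096 = 0.569 |
| W = 3 | 2 × 5 / 1024 = 0.010 | W = 14: 2 × 104 / 2048 = 0.102 | W = 26: 2 × 695 / 4096 = 0.339 |
| W = 0 | 2 × 1 / 1024 = 0.002 | W = 11: 2 × 55 / 2048 = 0.054 | not needed |

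The device works in both directions. If the added man stopped in the placebo session, his rank counts for caffeine, W stays at 8, and p = 2 × 25 / 2048 = 0.024.

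**The case against.** A reader might infer that the completers are selected for a good response to caffeine and that the result is therefore tilted towards benefit. The documents do not support that.

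- Low power output is never a ground for withdrawal. Non-responders, and men whose performance falls, finish and are analysed. The ground is intolerance, and the link from intolerance to poorer performance is an inference.
- Withdrawal is decided blind (6.2.2) unless the code is broken under 6.3, so complaints in a placebo session can also remove men. That pushes the other way.
- Section 3.2 does not expect these side effects at the study dose, and known hypersensitivity is an exclusion (7.1). Such losses may be few. Section 3.7, however, allows that adverse effects can occur, and section 7.4 provides for them.
- Section 9.2.4 asks about tolerance 45 minutes after ingestion but does not say that the exercise test is withheld.
- The worst-rank figures show how severe the device is. When even ten out of ten in favour goes from 0.002 to 0.054, the movement says little about the true bias.
- Men covered by section 8.5 have at most one dosed session and could not enter a paired test. Serious adverse events are still documented in the case report forms (10.1).
- This is a pilot, and sensitivity analyses for missing data are often left to an analysis plan, which is not at hand.

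All of this limits the claim about bias, and most of it stands. It does not remove the contradictions on keeping data or within section 11.5. An analysis plan cannot repair destroyed data, and the pilot still tests primary hypotheses at the 5% level.

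**Conclusion.** The point holds in a limited form. Certain, without assumptions: section 8.5 contradicts sections 12.1.3 and 12.2.3, section 11.5 contradicts itself, and the primary power-output analysis applies to men who completed and tolerated the dose, because one withdrawal ground is tied to caffeine. Not established: that the result favours caffeine, or by how much. Under the assumed ranges, with no placebo-session withdrawals, the shift is 0 to 4 W. It is nil if intolerant men would have performed as well as the others, and it can reverse if placebo-session withdrawals dominate. The move from p = 0.049 to 0.24 with one worst-ranked man is a bound on what one excluded man could do among ten completers. It does not estimate what will happen. The change should be made, because following the text as written destroys information that would be needed to judge a treatment-related exclusion.

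**What to change.** 1. Delete the destruction sentence in section 8.5 and state that data of withdrawn men are kept under sections 12.1.3 and 12.2.3.
2. Reconcile the two sentences of section 11.5. For example, state that all collected data are kept and described, that the primary paired tests use men with both sessions, and that nothing is imputed in those tests.
3. Report every withdrawal after dosing by group, supplement letter (A or B), session and reason. Word the primary result as applying to men who completed the protocol and tolerated the dose.
4. Add one worst-rank sensitivity analysis of power output, labelled as a bound. A man who stops because of side effects is retained, and the session in which he stopped is ranked worst, by the same rule for both supplements. It can be run by letter before the code is opened.

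The withdrawal rule itself is unchanged. The cost is wording and one extra analysis. The downside is that the sensitivity result may be less favourable than the completers result.
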